## Methods and design

The main purpose of this study is to compare the safety and efficacy of evidence-based traditional Chinese medicine massage and External Diclofenac Diethylamine Emulgel in KOA patients. Three hundred participants will be recruited for the study. Clinical data measurements, X-rays, and MRI scans will be evaluated at baseline and the end of treatment (Fig. 1). The study has been approved by the ethical committees of Guang’anmen Hospital (NO:201-135-KY-1) and registered in the Chinese Clinical Trial Registry (http://www.chictr.org.cn/showproj.aspx?proj=24457). The registration number is ChiCTR1800014400. The protocol will be reported following Standard Protocol Items: Recommendations for Interventional Trials (SPIRIT) statement.

**Fig. 1 Fig1:**
[figure not shown]
Schedule of enrollment,intervention, and assessment

### Study setting and recruitment

The study will be carried out at the five hospitals: Guang’anmen Hospital, Beijing’s Capital Medical University Traditional Chinese Medicine Hospital, Dongfang Hospital of Beijing University of Chinese Medicine, Xuan Wu TCM Hospital Beijing, and Beijing Fengsheng Trauma-Orthopedic Hospital of Traditional Chinese Medicine. The study will recruit participants with KOA who meet the diagnostic criteria of the American College of Rheumatology through hospital outpatient [16]. WeChat official account is one of the Chinese popular social media platforms of Guang’anmen Hospital and brochures. Meanwhile, the recruitment of participants has started in June 2018.

### Participants

#### Inclusion criteria

The following are the inclusion criteria:Meet the diagnostic criteria of knee osteoarthritis according to the American College of Rheumatology (ACR) criteria [16].Patients who have WOMAC pain scores of 25 or more out of 100 will be included.K-L classification ≥ 1 [17].Age 40–80 years, male or female.Signed informed consent.If the patient has two affected knees of which only one meets the ACR criterion and Kellgren-Lawrence grade II or III [16], only this knee will be evaluated. In the case that both knees are affected in accordance with the inclusion criteria (ACR and Kellgren-Lawrence grade II or III), the more painful knee will be chosen for evaluation.

#### Excluded cases criteria

The following are the exclusion criteria:Patients with secondary osteoarthritisPatients with obvious unstable knee joint (ACL, PCL, MCL injury) [18–20]Patients who have received intra-articular injection of sodium hyaluronate or hormoneList excluding comorbidities: severe osteoporosis, diabetes, lower extremity vascular disease, limb malformation or nerve system disease, severe mental illness, unable to understand others’ intentions or express themselves correctlyPregnant women and those trying to conceive or currently breastfeedingPatients who have combined heart, lung, brain, liver, kidney, and hematopoietic system and other serious diseasesPatients who have a contraindication for MRIPatients who have an allergy history for investigational products and have an allergic constitutionPatients who are participating in other clinical trialsPatients who have been used to alcoholic and/or psychoactive drug substances, drug abuser, and relierAccording to the researchers’ judgment, other diseases or conditions that may reduce the possibility or complicate the inclusion, such as frequent changes in the work environment and unstable living environment, which may easily lead to loss of follow-up

#### Dropout criteria

Participants who do not complete the clinical protocol for the following reasons should be considered as dropped out:The patient quits (poor efficacy or adverse reactions).Loss to follow-up.Researchers remove the patient (poor compliance or serious adverse events).

#### Comprehensive suspension criteria

The trial will be suspended if:The investigators discover a significant safety problem.The therapeutic effect is poor (we will assess the therapeutic effect in week 5).There is a major mistake in the plan.The sponsor has a huge problem in funding or management.

### Informed consent and participant safety

Participants will be required to sign an informed consent and have the same chance to receive appropriate treatment. The safety of participants will be monitored in every visit. Two attending physicians and two responsible joint care specialists will be responsible for the collaboration and guidance of clinicians during each clinical trial and implementation. The two chief joint surgeons constitute the endpoints Adjudication Committee, which is responsible for the overall supervision of the clinical trials.

During the treatment, any adverse events, such as local skin dryness, skin irritation, fracture, dislocation, or increased pain should be recorded and reported to the relevant responsible unit and the ethics committee in time. If the adverse events such as death, fractures, and organs injury are confirmed to be related to the study, the Ethics Committee of Guang’anmen Hospital, China Academy of Chinese Medical Sciences, has the right to discontinue or modify allocated interventions. If an adverse event occurs during the clinical trial, medical experts will be engaged to assess and investigate the actual cause, and medical and financial compensation will be made to participants. If the participants cannot tolerate these adverse reactions, treatment will be discontinued and the participants will be withdrawn from the study.

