## Introduction

Knee osteoarthritis (KOA) ranks highly among global causes of disability and chronic pain, particularly in people over 50 years of age [1]. Structured exercise programs, dietary weight management, and mind-body exercise (such as tai chi and yoga) were considered by the panel to be effective and safe for all patients with knee OA [2–5]. These updated OARSI guidelines recommended non-pharmacological as the core treatments for KOA in all cases [6].

Massage is a safe and non-pharmacological treatment with limited contraindications and no known serious adverse events [7]. Traditional Chinese massage has a positive effect on KOA and widely used in China. In recent several studies have shown that Chinese massage therapy decreased pain and may improve extensor muscle strength, and it may improve walking ability for these KOA patients; however, different massage sects in China caused assessment difficulties for the treatment of KOA [8, 9]. In order to standardize massage techniques and procedures, we organized multi-disciplinary experts in China to conduct a questionnaire survey and field discussions and successfully acquire an evidence-based traditional Chinese medicine massage treatment of knee osteoarthritis [10].

Topically administered non-steroidal anti-inflammatory drugs (NSAIDs) such as Diclofenac solution attained significantly greater improvement in pain reduction in patients with KOA and are widely used in the world [11–14]. However, local skin reactions happened more commonly in patients treated with topical NSAIDs [15].

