### Outcomes

The efficacy between the two groups will be assessed by primary outcome measure: change in WOMAC score three times (week 0, week 5, week10) (Fig. 1). The secondary outcomes measured at three time points (week 0, week 5, week10) included the Chinese Scale for Knee Osteoarthritis (CSKO), and at two points (week 0, week10) included *X-ray and MRI*.

In order to observe the time to effect, we measure the primary and secondary outcomes at week 5 and week 10, respectively; however, only the clinical results of week 10 were used as the final evaluation outcomes.

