### Safety outcomes

(1) Vital signs: body temperature, resting heart rate, respiratory, and blood pressure after 10 min of rest (systolic blood pressure, diastolic blood pressure). (2) Laboratory examination: blood routine (RBC, WBC, platelet, hemoglobin), urine routines (urine red cell, LEU, urinary protein, glycated hemoglobin alc), stool routine+occult blood, and liver function (ALT, AST), and renal function (BUN, Cr, 12 lead routine electrocardiogram). (3) Manipulation-related adverse events, such as ecchymosis, subcutaneous hemorrhage, fracture, and dislocation. (4) Drug-related adverse events, such as gastrointestinal tract response. (5) Other adverse events.

The safety of each therapy was evaluated by comparing the changes in blood and urine routine, liver and kidney function, electrocardiography before and after the treatment, and the incidence of adverse events during the treatment.

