### Statistical analysis

All statistical analyses will be performed with the SPSS software (SPSS 20.0, SPSS Inc., Chicago, IL, USA) by statisticians who are independent of the research team and blinded to the group allocation. Data analysis will be based on the intention-to-treat (ITT) principles. All numerical data will be presented as the mean ± SD, and categorical variables will be described with percentages (%). All the statistical tests are bilateral inspection; *p* < 0.05 is considered statistically significant. Paired *t* test or the paired rank sum test is used for the comparison within the groups; the *χ*^2^ test or Fisher’s exact probability method is used for the count data, and the Wilcoxon rank sum test is used for the rank data between groups. CMH *χ*^2^ test is used for the primary outcome of WOMAC improve rate. It is necessary to adjust the baseline and centers of the changes in WOMAC score between the groups with the covariance method.

The secondary outcome includes CSKO score, X-ray data, and MRI data, which are all measurement data, and a group *t*-test or the Wilcoxon rank-sum test is used for comparison between the groups. The *χ*^2^ test or Fisher’s exact probability method is used for participants’ dropout and adverse events rate analysis.

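### Stopping treatment for an intolerable adverse reaction also removes the participant from the study, which undercuts the stated intention-to-treat analysis

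*Protocol article*

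**What the plan says.** All references are to the protocol article.

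- **Informed consent and participant safety** gives the rule for intolerable reactions: "If the participants cannot tolerate these adverse reactions, treatment will be discontinued and the participants will be withdrawn from the study". The same section indicates which events are meant: "any adverse events, such as local skin dryness, skin irritation, fracture, dislocation, or increased pain should be recorded".
- **Dropout criteria** counts as a dropout the case "The patient quits (poor efficacy or adverse reactions". It also counts patients whom the researchers remove and, as a separate entry, patients lost to follow-up.
- **Outcomes** schedules WOMAC at weeks 0, 5 and 10, but "only the clinical results of week 10 were used as the final evaluation outcomes".
- **Statistical analysis** states: "Data analysis will be based on the intention-to-treat (ITT) principles". It plans a test of WOMAC improvement rates and a covariance analysis of WOMAC change adjusted for baseline and centre. Dropout appears there only as something to compare between groups, in the "dropout and adverse events rate analysis".

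Nothing in the article provides for assessing a participant after study treatment has stopped.

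**The concern.** An intention-to-treat analysis compares the groups as randomised, whether or not treatment was completed, so it relies on outcomes from patients who stopped. The withdrawal rule works against this. It is triggered by intolerance, not by the participant withdrawing consent, so it gives up scores that could have been obtained.

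The patients lost are unlikely to be a random subset. Increased pain is one of the listed events, and pain is part of WOMAC. The arms also have different reaction profiles. For massage, Safety outcomes lists "Manipulation-related adverse events, such as ecchymosis, subcutaneous hemorrhage, fracture, and dislocation". For the gel, the Introduction says that "local skin reactions happened more commonly in patients treated with topical NSAIDs". Participants know their treatment (Blinding), so willingness to tolerate a reaction may itself differ by arm. The net direction cannot be predicted.

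A score that was never collected can only be assumed. How missing scores are analysed may properly be left to the analysis plan and is not at issue here. No analysis plan can recover them, and a between-group test of dropout rates would show an imbalance without correcting it.

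**Working it through.** **Step 1. Follow the rule through the schedule.** A participant removed after week 5 but before week 10 has a week-5 WOMAC and no final one. A participant removed before week 5 has no WOMAC after baseline. Both belong to the intention-to-treat population.

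**Step 2. Reproduce the plan's own figure.** Sample size gives response rates of 95.6% (massage) and 79.8% (gel) and a minimum of 85.49 per group. Power is not stated; 90% is assumed here, with two-sided 5% significance:

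n = (z₀.₉₇₅ + z₀.₉₀)² × [p₁(1−p₁) + p₂(1−p₂)] / (p₁−p₂)²

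= 10.5 × (0.956×0.044 + 0.798×0.202) / 0.158² = 10.5 × 0.20326 / 0.024964 = 85.49

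(85.55 without rounding the constant to 10.5). The sample size is not in question.

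**Step 3. Outer bounds on the all-randomised difference.** The documents give no withdrawal rate, so all rates here are assumed. Let w be the share of an arm withdrawn, and let p be the response rate in percent among patients with a week-10 score, set to the planning rates. If no withdrawn patient responds, the arm rate is p(1−w). If all do, it is p(1−w) + 100w. The lower bound of the difference is massage low minus gel high, and the upper bound is massage high minus gel low. The width is 100(w_massage + w_gel).

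| Withdrawn, massage / gel | Massage rate (%) | Gel rate (%) | Difference (points) | Width |
|---|---|---|---|---|
| 2% / 2% | 93.69 to 95.69 | 78.20 to 80.20 | 13.5 to 17.5 | 4 |
| 5% / 5% | 90.82 to 95.82 | 75.81 to 80.81 | 10.0 to 20.0 | 10 |
| 10% / 5% | 86.04 to 96.04 | 75.81 to 80.81 | 5.2 to 20.2 | 15 |
| 5% / 10% | 90.82 to 95.82 | 71.82 to 81.82 | 9.0 to 24.0 | 15 |
| 10% / 10% | 86.04 to 96.04 | 71.82 to 81.82 | 4.2 to 24.2 | 20 |

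**Step 4. Direction.** Now let 79.8% of scored patients respond in both arms.

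- 10% of massage (20 of 200) and 5% of gel (5 of 100) withdrawn: counting them as non-responders gives 79.8×0.90 − 79.8×0.95 = 71.82 − 75.81 = −4.0 points.
- 5% of massage (10 of 200) and 10% of gel (10 of 100) withdrawn: 75.81 − 71.82 = +4.0 points.
- Using scored patients only gives 79.8 − 79.8 = 0 in both cases.
- With equal withdrawal rates, both approaches give 0.

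Without the scores, the data cannot show which answer is right.

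**Step 5. Power.** Two-sided 5% two-proportion test with pooled variance under the null, 95.6% against 79.8%:

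| Lost per arm | Patients (massage/gel) | Power |
|---|---|---|
| none | 200/100 | 97.9% |
| 2% | 196/98 | 97.7% |
| 5% | 190/95 | 97.4% |
| 10% | 180/90 | 96.8% |

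The issue is bias, not power.

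**The case against.** The strongest counter-argument is that the harm is inferred. The article does not say that withdrawn participants go unassessed. Dropout criteria lists loss to follow-up separately from quitting and removal, so being a dropout need not mean having no week-10 score. The article condenses a fuller protocol (Data Availability) that might provide for continued assessment. This stands as a reason for caution, and it weakens Dropout criteria as supporting evidence. It does not change the withdrawal sentence, which names leaving the study as a consequence over and above stopping treatment. If the full protocol says otherwise, the article's sentence still needs correcting.

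Second, Experimental group provides loxoprofen as rescue for intolerable knee pain, and Control group makes other care similar. This should reduce pain-related withdrawal. It does not abolish it, and it does not address skin or manipulation reactions, although their link to WOMAC is weaker.

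Third, counting withdrawn patients as non-responders is a legitimate all-randomised analysis that needs no later score. That is true for the responder endpoint, so intention-to-treat is weakened and not made impossible. But it remains an assumption, and it does not serve the adjusted analysis of WOMAC change.

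Fourth, every rate is assumed, the bounds would apply to missing data from any cause, and massage stays ahead throughout the Step 3 table. All of this is correct. Massage stays ahead there because the planning rates start 15.8 points apart. The hypothesis is non-inferiority, so the equal-response case in Step 4 is also relevant, and there the sign depends on the assumption. Nothing in the documents shows that withdrawals will be as frequent as 10%, and the Introduction describes massage as having no known serious adverse events.

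**Conclusion.** The concern holds. As written, the rule discards primary-outcome scores for reasons tied to treatment, in a trial that declares an intention-to-treat analysis and judges efficacy at week 10 alone. It is a stated rule, not a detail left to another document.

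The size is unknown. Under the assumed rates, the all-randomised difference is left undetermined by 4 points at 2% withdrawn per arm, 10 points at 5% and 20 points at 10%. A five-point imbalance in withdrawal can move an equal-response result by 4.0 points either way, depending on how the missing patients are counted. If withdrawals are few and balanced, the effect is small.

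The conclusion rests on reading removal from the study in its ordinary sense, as the end of assessment. Confidence is therefore medium. The rule should be fixed, but it does not invalidate the trial.

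**What to change.** In Informed consent and participant safety, replace removal from the study with discontinuation of study treatment only. State that the week-5 and week-10 WOMAC will be collected from every randomised participant who has not withdrawn consent. This also covers patients who quit treatment or are taken off it under Dropout criteria, and the wording there should be aligned. The right to stop treatment for an intolerable reaction is unchanged.

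The cost is a wording amendment and WOMAC follow-up of the patients who stopped treatment. No extra patients are needed.

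Trial status predicted the end of recruitment by September 2021, so follow-up may be complete. In that case, collect only the scores that can still be obtained, and report the number lost per arm under this rule as a limitation.

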### Randomization

In this study, this clinical research adopts randomized blocks, and cases will be randomly assigned to each center. The results of the random groups will be placed in sealed envelopes, which are numbered consecutively. When the patients are enrolled, they take the envelopes in the order of enrollment and will be grouped according to the contents of the envelopes. In the waiting list group, in a ratio of 2:1, there are 200 cases in the experimental group and 100 cases in the control group. The random sequence will be generated by an independent professional statistician who is not involved in the study with the SPSS software (SPSS 20.0, SPSS Inc., Chicago, IL, USA). The random numbers will be stored by a fixed non-involved person.

### Blinding

Due to the operation characteristics of massage therapists, the massage therapists and the participants cannot be blinded who will be informed of the grouping of participants before treatment; however, massage therapists will be blinded to pain and function scores, as well as baseline imaging results. Participants will be told that they will randomly receive one of the interventions after enrollment. The outcome evaluators and data statisticians will be blinded to the group allocation, and their responsibility is to collect and analyze the data.

### Sample size

According to the literature, the average effective rate of treating knee osteoarthritis only through massage is 95.6% and 79.8% by application of external diclofenac diethylamine emulsion latex [15]. According to the sample size calculation formula, the minimum sample size of each group is *n* = 85.49. Considering expulsion case and getting significant results, at the same time, in order to implement layered research in the experimental group, we planned the ratio of the cases in the experimental group and the control group is 2:1, and the number of included cases was 300. There were 200 cases in the experimental group, and 100 cases were in the control group.

### Interventions

#### Experimental group

Two hundred patients in the experimental group will receive 20 sessions of manual massage treatment (2 sessions weekly for 10 weeks,10 min one session). Use the definite evidence-based traditional Chinese medicine massage technique for knee osteoarthritis to do the massage treatment [10].

During the treatment period, other Chinese and Western drugs and treatment methods (including physical therapy and psychotherapy, etc.) for knee osteoarthritis are not used. In cases of intolerable knee pain, the patients will be instructed to take loxoprofen sodium tablets (60 mg, oral 3/day) as a rescue medication. The use of other treatments, such as injections of any kind, moxibustion, acupuncture, or cupping, will not be allowed.

When combined with other diseases, the drugs and treatments must be continued, and the drugs and treatments need to be recorded in detail in the combined medication list.

#### Control group

One hundred patients in the control group will receive External Diclofenac Diethylamine Emulgel (Beijing Novartis Pharma Ltd. producing, trade name: Vitalin Emulgel) treatment (3–4 times per day for 10 weeks). Other interventions will be similar to the experimental group.

### Trial conduct

The personnel participating in the clinical trial shall accept the coincident training and then conduct the clinical trial after passing the examination. The radiologists and doctors will accept the training in filmmaking and reading. All MRI examinations and measurements are completed by Guang’anmen Hospital, Chinese Academy of Traditional Chinese medicine. The main investigator refers to the drug administrator who specifically supervises the study. The drug administrator shall keep records of drug receipt, distribution, and return. The quality inspectors will monitor the drug tablet return and laboratory tests, then write the audit report and submit it to the project team leader every month. The project management group is responsible for checking the research quality and progress of the subcenter every 3 months. Modifications to the protocol will be submitted to the Ethics Committee of Guang’anmen Hospital to review, and audits will be held annually by the Ethics Committee. The above process will be independent from investigators and the sponsor.

### Outcomes

The efficacy between the two groups will be assessed by primary outcome measure: change in WOMAC score three times (week 0, week 5, week10) (Fig. 1). The secondary outcomes measured at three time points (week 0, week 5, week10) included the Chinese Scale for Knee Osteoarthritis (CSKO), and at two points (week 0, week10) included *X-ray and MRI*.

In order to observe the time to effect, we measure the primary and secondary outcomes at week 5 and week 10, respectively; however, only the clinical results of week 10 were used as the final evaluation outcomes.

#### Primary outcome

##### The Western Ontario and McMaster Universities Osteoarthritis Index (WOMAC)

WOMAC score was performed for each follow-up, with the calculation of the total score of WOMAC, and each dimension was compared before and after treatment [21]. Clinical recovery: WOMAC score reduction by 95%; excellent: WOMAC score reduction by 70%; efficient: WOMAC score reduction by 30%; inefficient: WOMAC score reduction less than 30%. Note: the calculation formula [(WOMAC score before treatment − WOMAC score after treatment)/WOMAC score before treatment] × 100%.

